**Perform baseline assessment**

**Allocation**

**Control Group**

20 subjects

**Experimental Group**

20 subjects

**6 weeks intervention**

Conventional rehabilitation=60 min/day

**6 weeks intervention**

Leap motion control rehabilitation=30 min/day

**Perform post treatment assessment**

**Statistical Analysis**

**Participants:**

Inclusion criteria are as follows:

1. Age 18-50 years, who have been referred from the Dept. of Orthopaedic.
2. Patients must be diagnosed with an A3 extraarticular multi-fragmentary distal radial fracture type and treated conservatively with plaster cast immobilization and closed reduction.
3. Participants must accept and sign the Informed consent.
4. No previous history of wrist/ hand fracture, history of inflammatory arthritis, or any possible upper limb fracture.
5. Patients who are able to comprehend (Lyngcoln et al., 2005).

Exclusion criteria are as follows:

1. Participants who were treated for DRF reduction and/or fixation with some form of surgical intervention (e.g. external fixation, volar plate, and Kirschner wires).
2. Patients with Mini-Mental score less than 26 points on the examination.
3. After the removal of the immobilization, patients with immediate complications like malunion or non-union.
4. Patients with past trauma either in arms or hands that had impaired function.
5. Patients with inflammatory or non-inflammatory diseases and neurological disorder were excluded.

**Sample size consideration:** This is an experimental study with two-group design that examines the effect of leap motion control in distal radial fracture rehabilitation. Analysis of previous power using G*Power is used to determine the same size (Engel et al., 2019). 40 participants will be enrolled to the control group or experimental group and will be allocated accordingly (Maciel et al., 2005). The G*Power analysis followed the following terms for calculation of sample size which is graphical represented in figure 2.

**t tests** - Means: Difference between two independent means (two groups)

**Analysis:** A priori: Compute required sample size

**Input:** Tail(s) = One

Effect size d = 0.8

α err prob = 0.2

Power (1-β err prob) = 0.95

Allocation ratio N2/N1 = 1

**Output:** Non-centrality parameter δ = 2.5298221

Critical t = 0.8511828

Df = 38

Sample size group 1 = 20

Sample size group 2 = 20

Total sample size = 40

Actual power = 0.9531573

**Figure 2:** The calculation of sample size using G*Power analysis

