In younger people, DRF is mostly associated with fall associated during sports events and road traffic accidents (Burhani and Naqvi, 2020). The incidence of DRF in females is significantly greater than in males incorporating the menopause as responsible factor leading to osteoporosis associated with reduced bone density showing peak between the age group of 60 and 70 (Gutiérrez-Espinoza et al., 2017).

Considering the injury patterns and patient profiles being heterogenous in nature, the management line should prefer the severity of the injury, the desired functional independency of patients along with existing comorbidities. In older adults, the preferred line of management is conservative or non-operative to have good results with foundation stone of immobilisation. Surgical management options include closed reduction and application of a cast, percutaneous K-wires, open reduction and internal fixation with plates, or external fixation according to the patient requirements (Vaghela et al., 2020). Following DRF, many factors manipulate the recovery of the patient implying the age, gender, site and extent of injury, management line followed to manage the respective injury, compensations, patient’s education regarding the condition, radial shortening, and intra-articular involvement (Björk et al., 2020). Patients generally recover within 3-6 months to maximum range of motion, strength and function whether managed conservatively or surgically.

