Patients with DRF after a duration of immobilisation are often referred for physiotherapy. In the clinical setting physiotherapists use disability assessment, such as range of motion and grip strength, to determine progress as well as outcomes. Hand activity requires a combination of adequate sensation, proprioception, intact neurological control and coordination, appropriate anatomical alignment, and muscle strength and flexibility (Gutiérrez-Espinoza et al., 2017). Physiotherapy interventions are techniques used to improve functional recovery following a distal radial fracture (Bruder et al., 2013). Physical therapy (PT) is of critical importance after the immobilization phase. PT is recommended for reducing pain, increasing range of motion (ROM) and enhancing muscle function and muscle strength. Early rehabilitation concentrate on oedema management, pain reduction as well as shoulder and finger motions (Björk et al., 2020). The therapeutic methods applied to attain these goals may be categorized as active or passive methods. Active treatment includes approaches in which patients has to participate actively in their treatment, such as counselling, a home exercise program (HEP), or supervised programme by a physiotherapist (Smith et al., 2004). Passive treatments relate to interventions where the patient plays a passive part during its procedure, such as mobilization of joint (JM), massage and the use of hot pack, TENS and ultrasound (Maciel et al., 2005).

The use of virtual reality (VR) technology platform in a healthcare environment has become increasingly common over the last two decades. This was rooted in clinical practice. The introduction of VR technology into traditional training has the ability to further increase the outcomes of the training. VR allows users to actively interact in real-time with a simulated environment and offers the opportunity to practice skills learned in the virtual environments to everyday life (Huang et al., 2019). VR-based training has the ability to promote implicit learning, improve variety, and involve the patient actively during the training. Such characteristics are crucial in the optimization of motor learning and could maximize the training impact.

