**Statistical analysis:** The SPSS latest version will be used to perform statistical analysis. To compare the group effect, two-way repeated measures ANOVA (analysis of variance) will be used. When ANOVA reveals a significant difference, student’s t test will be used to compare the changes within the group. Statistical significance is determined by a two-sided p value of less than 0.05. Mann-Whitney U, t-test or Fisher’s exact test will be used for comparing Groups at baseline and for comparing the primary and secondary outcomes between the groups at 6 weeks.

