**Scope:**

Leap motion tracking device is an innovative technique which may be used in initial period of rehabilitation for early recovery in distal radial fracture. Also, the studies concentrating on the effectiveness of Leap motion tracking device is limited making it difficult to conclude as an intervention in DRF. Hence, it is necessary to conduct a new experimental study with more standardization in type of intervention and treatment protocol along with larger samples focusing on the effectiveness of leap motion tracking device.

**Implication:** In the present study it can be implied that, Leap motion tracking device based therapy can be an important technique used regularly for the patients with distal radial fracture.

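### Eligibility sets no maximum time since fracture or cast removal, although the protocol expects recovery within 3-6 months and aims the device at early rehabilitation

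*Protocol*

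**What the plan says.** Under Participants, the Protocol lists five inclusion and five exclusion criteria. Those closest to this point are:

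- Age and source of referral: "Age 18-50 years, who have been referred from the Dept. of Orthopaedic". This says who refers the patient, not when.
- Fracture and treatment: "Patients must be diagnosed with an A3 extraarticular multi-fragmentary distal radial fracture type and treated conservatively with plaster cast immobilization and closed reduction".
- An exclusion that mentions the cast: "After the removal of the immobilization, patients with immediate complications like malunion or non-union". It implies entry after cast removal but gives no number of days or weeks.

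Three background statements bear on timing. The Introduction says "Patients with DRF after a duration of immobilisation are often referred for physiotherapy", and also "Patients generally recover within 3-6 months to maximum range of motion, strength and function whether managed conservatively or surgically". The Scope says "Leap motion tracking device is an innovative technique which may be used in initial period of rehabilitation for early recovery in distal radial fracture". None of them is an eligibility rule.

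Under Study design, 40 patients are randomised 1:1 and no stratification is stated. The Statistical analysis paragraph names a two-way repeated measures ANOVA. For the comparison of the two arms at the 6-week assessment, it then states: "Mann-Whitney U, t-test or Fisher’s exact test will be used for comparing Groups at baseline and for comparing the primary and secondary outcomes between the". Neither method is given a term for elapsed time.

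**The concern.** The outcomes (DASH, range of motion, grip strength, pain) are largely those the Protocol expects to improve over the months after the injury whichever way it is managed. How much a patient can still gain during a 6-week programme then depends on how far recovery has gone at entry. With no limit on that time, a patient whose cast has just come off and one referred months later are equally eligible.

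Four things are at stake:

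- **Variance.** Mixed recovery stages widen the spread of 6-week outcomes and of change from baseline.
- **Dilution.** Patients with little left to gain pull the difference between arms toward zero.
- **Chance imbalance.** With 20 per arm, the mean time since cast removal can differ between arms by chance, and an unadjusted comparison carries that difference into its estimate.
- **Population.** The Scope speaks of the early phase of rehabilitation, but the criteria do not confine entry to it.

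**Working it through.** **1. The Protocol's own figure.** Inputs from the sample size section: d = 0.8, one-sided alpha 0.2, 20 per group. The non-centrality is 0.8 × √(20/2) = 2.530, the critical t on 38 degrees of freedom is 0.851, and the power is 0.953. This matches the stated 0.9531573; 19 per group would give 0.947. The figure reproduces, but none of its inputs concerns time since fracture, so it neither supports nor answers the point.

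**2. Search of the criteria.** None of the ten gives a minimum or maximum time since fracture, cast removal or start of rehabilitation. The gap is a matter of text, not of arithmetic.

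**3. Chance imbalance in mean entry time.** With 20 per arm and no stratification, the SE of the arm difference is SD × √(2/20) = 0.316 SD, so the 95% range is ±1.96 × 0.316 = ±0.62 SD. To put this in weeks, assume (not in the Protocol) that entry is spread evenly over 0 to w weeks after cast removal, so SD = w/√12:

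| w (weeks) | SD | SE of arm difference | 95% range |
| --- | --- | --- | --- |
| 12 | 3.46 | 1.10 | about ±2.1 |
| 2 | 0.58 | 0.18 | ±0.36 |

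For w = 12, the chance that the imbalance exceeds 1 week in either direction is P(|Z| > 1/1.10) = 36%. These are weeks of entry time. The Protocol gives nothing with which to turn them into DASH points, degrees, grip strength or pain.

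**4. Dilution.** Assume (not in the Protocol) that a share f of patients can gain nothing from either programme and that the SD is unchanged. Then d = 0.8 × (1 − f). Power with 20 per group:

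| f | d | one-sided 0.2 (sample size) | two-sided 0.05 (analysis) |
| --- | --- | --- | --- |
| 0 | 0.80 | 0.95 | 0.69 |
| 0.1 | 0.72 | 0.92 | 0.60 |
| 0.2 | 0.64 | 0.88 | 0.51 |
| 0.3 | 0.56 | 0.82 | 0.41 |

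**5. Added variance.** Assume (not in the Protocol) that 0.8 applies to patients at a similar stage and that entry time adds a share R² of the total variance. Then d = 0.8 × √(1 − R²):

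| R² | d | one-sided 0.2 | two-sided 0.05 |
| --- | --- | --- | --- |
| 0.1 | 0.76 | 0.94 | 0.65 |
| 0.3 | 0.67 | 0.90 | 0.54 |
| 0.5 | 0.57 | 0.83 | 0.41 |

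If 0.8 already reflects a mixed population, this loss is already counted. The Protocol does not say.

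The drop from 0.95 to 0.69 with no dilution comes from the different alpha levels in the sample size and analysis sections. That is a separate matter and no part of this point.

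**The case against.** A reader might infer that patients who have already finished recovering will be enrolled. The Protocol does not show this. Orthopaedic referral, the exclusion worded around cast removal and immediate complications, the Introduction's account of referral after immobilisation, and the graded start of the Group A programme all suggest early entry. They make late entry less likely, but none of them sets a limit.

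A reader might also infer that the allocation leaves time since cast removal unbalanced and so biases the comparison. It does not: randomisation balances that time in expectation, and the error rate of the between-group test already allows for chance imbalance. What remains is lost precision and dilution.

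The repeated measures ANOVA uses the baseline assessment and therefore absorbs part of the difference in starting level. It does not remove differences in the recovery still to come, and the separate 6-week tests adjust for nothing.

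The illustrations in weeks and in plateau share have no source in the Protocol and should not be combined. If the 3-6 months run from cast removal, almost nobody entering within 12 weeks has reached even the lower end. If they run from the fracture, the length of casting is needed, and it is not given.

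A covariate may be left to a statistical analysis plan, and the two dates may already be on the case history form, which is not reproduced. Neither is counted here as an omission. An entry window, however, belongs among the eligibility criteria. A broad population could be deliberate, since the Aim is not restricted to early patients, but it would then fit poorly with the Scope.

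**Conclusion.** The point holds as a cheap improvement. The criteria permit entry at any time after fracture or cast removal, while the Protocol's own text makes that time relevant to its outcomes and to the intended use of the device. The consequences are added variance, possible dilution, chance imbalance that the 6-week tests do not remove and the ANOVA removes only in part, and some doubt about which patients the result describes. They do not include systematic bias or an inflated type I error.

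The size of the loss cannot be derived from the Protocol. The ±2.1 weeks rests on an assumed 0-12 week spread, d of 0.72 to 0.56 on an assumed 10-30% of patients with nothing to gain, and the R² figures on an assumed share of variance. It would go too far to read any of them as a forecast for this trial.

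**What to change.** - Add one inclusion criterion: the baseline assessment takes place within a stated maximum time since cast removal. The investigators should choose that time to match what they mean by the early phase of rehabilitation; the Protocol offers no figure to take over.
- Record the dates of fracture and of cast removal at baseline, if the case history form does not already do so.
- In the 6-week between-group comparison, include time since cast removal and the baseline value of the outcome as covariates, and state this before enrolment.

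Cost: one eligibility line, two dates, and two of the 38 error degrees of freedom. Some late referrals would become ineligible from an already narrow single-centre pool (one fracture type, conservative treatment, ages 18-50), so recruitment may slow by an amount the Protocol does not allow one to estimate. If that is unacceptable, the dates and the covariates alone can still improve precision at almost no cost, and the report can describe when patients actually entered.

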**Outcome measures:**

Primary outcome measure:

1. Disabilities of the Arm, Shoulder, and Hand Outcome Questionnaire (DASH): It is a 30- item questionnaire that evaluates the patient’s ability to perform upper extremity activities for functionality.
2. Universal goniometer for ROM: Active flexion and extension, radial deviation, ulnar deviation, pronation and supination of the wrist will be measured by a goniometer. Participants will be assessed to expose their arms in a seated position and to remove any accessories (Tremayne et al., 2002).

Secondary outcome measure:

1. Grip strength : To check grip strength a Jamar dynamometer will be used. The participants would be tested in sitting position with the arm and shoulder in neutral position and elbow in 90 degrees of flexion, and neutral forearm (Tremayne et al., 2002). Then, subjects will be asked with all their strength to make tight fists to maintain that position for 4 seconds and then rest for 30 seconds. First, the unaffected side will be tested and then affected side will be tested. The maximum value obtained from 3 trials will be recorded.
2. VAS: The visual analogue scale is a measurement scale for pain, consisting straight line of 10 cm, the left edge shows “no pain” and the right edge shows the “worst pain”. The subjects will be asked to draw a straight line illustrating the severity of the pain felt during the assessment.

**Follow up:** All patients will be followed up at 6 weeks after rehabilitation and follow-up record forms will be completed. The time of the last rehabilitation training session will be recorded. Electronic follow-up rehabilitation records will be preserved. When patients drop out of the trial, the reasons for withdrawal will be recorded in detail. Comprehensive and supportive patient communication will be undertaken; patients lost to follow-up because of any reason will be got in touch as soon as possible and be followed up within 6 weeks. Data regarding patients withdrawal from the study.

**Data management:** Data from the trial will be kept in a secure, locked storage area with limited access for later review by a biostatistician, a researcher in charge.

**Power analysis:** With G*power analysis, the sample size in respective group is calculated to be 20 patients with 95% confidence interval, power of 0.95 and effect size of 0.8. Therefore 20 patients in both groups have to complete 6 weeks of follow-up to have adequate statistical power.

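### The 0.95 power belongs to a t test at one-sided alpha 0.2, while the analysis plan tests at two-sided 0.05 and leaves two between-group tests unranked, one of which dilutes the treatment difference if read literally

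*Protocol*

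**What the plan says.** The Sample size consideration paragraph gives the G*Power inputs. The test is "Difference between two independent means (two groups", one-tailed, with "Effect size d = 0.8", "α err prob = 0.2", "Power (1-β err prob) = 0.95" and "Allocation ratio N2/N1 = 1". The output is 20 per group, 38 degrees of freedom and actual power 0.9531573. The effect size is not tied to an outcome or a time point.

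The Power analysis paragraph describes the same calculation as made "with 95% confidence interval, power of 0.95 and effect size of 0.8". It does not repeat the one-sided alpha of 0.2.

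The Statistical analysis paragraph says: "To compare the group effect, two-way repeated measures ANOVA (analysis of variance) will be used". A significant ANOVA then leads to t tests of change within a group. The threshold follows: "Statistical significance is determined by a two-sided p value of less than 0.05". The paragraph ends with a second between-group analysis: a Mann-Whitney U, t or Fisher's exact test, used to compare the groups at baseline and to compare the primary and secondary outcomes at 6 weeks.

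The protocol does not say which of the two between-group analyses is primary, or which ANOVA term carries the treatment comparison. It gives no baseline-to-6-week correlation.

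**The concern.** The power statement and the analysis do not describe the same test. There are two separate mismatches.

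- **Alpha and sidedness.** The trial is sized at one-sided 0.2 and analysed at two-sided 0.05. This affects every between-group test in the plan.
- **The term tested.** In a group-by-time ANOVA with a baseline and one later value, the group main effect compares each patient's average of the two values. Randomisation makes the expected baseline difference zero, so a difference that exists only at 6 weeks is halved by the averaging. The treatment effect sits in the group-by-time term, or in the comparison at 6 weeks.

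Two things are at stake. The ANOVA and the 6-week test can disagree on the same outcome, and nothing in the protocol says which one counts. In addition, the alternate hypothesis covers both an equal and a superior result for the device, so a non-significant group effect from a weak test could be read as support for equality.

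**Working it through.** **Inputs from the protocol.** 20 per group, d = 0.8, one-sided alpha 0.2 for sizing, two-sided 0.05 for analysis.

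**Assumptions.** The documents do not fix these: d = 0.8 applies at 6 weeks, no expected baseline difference, equal SDs, two time points (baseline and post-treatment, as in the flow chart), and baseline-to-6-week correlation r of 0.3, 0.5 or 0.7.

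**Step 1: reproduce the stated figure.** The noncentrality is d × √(n/2) = 0.8 × √10 = 2.530 on 38 df. At one-sided 0.2 the critical t is 0.851 and power is 0.953. This matches the protocol's output.

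**Step 2: change only the alpha.** With the same t test and noncentrality, at two-sided 0.05 the critical t is 2.024 and power is 0.693. This needs no correlation. A t test with 0.95 power at two-sided 0.05 would need 42 per group.

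**Step 3: standardised effect for each candidate test.**

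- Group main effect: the mean difference is 0.8/2 = 0.4 and the SD of a patient's average is √((1+r)/2), so the effect is 0.4/√((1+r)/2).
- Group-by-time: the difference in change is 0.8 and the SD of change is √(2(1−r)), so the effect is 0.8/√(2(1−r)).
- ANCOVA on the 6-week value: the residual SD is √(1−r²), so the effect is 0.8/√(1−r²).

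For example, at r = 0.5 the main effect is 0.4/√0.75 = 0.462. Its noncentrality is 0.462 × √10 = 1.461, and power at two-sided 0.05 is 0.296.

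**Step 4: power with 20 per group** (noncentral t, 38 df; 37 for ANCOVA).

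| Test | Alpha | r = 0.3 | r = 0.5 | r = 0.7 |
|---|---|---|---|---|
| 6-week t test | one-sided 0.2 | 0.95 | 0.95 | 0.95 |
| 6-week t test | two-sided 0.05 | 0.69 | 0.69 | 0.69 |
| Group main effect | one-sided 0.2 | 0.76 | 0.73 | 0.70 |
| Group main effect | two-sided 0.05 | 0.33 | 0.30 | 0.27 |
| Group-by-time | two-sided 0.05 | 0.55 | 0.69 | 0.89 |
| ANCOVA | two-sided 0.05 | 0.73 | 0.81 | 0.93 |

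Over r from 0 to 0.9 the main effect at two-sided 0.05 runs from 0.41 down to 0.24, so no correlation in that range brings it near 0.95.

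**Step 5: separate the two causes.** The alpha change alone takes the t test from 0.95 to 0.69. At two-sided 0.05, moving from the t test to the main effect takes power from 0.69 to between 0.33 and 0.27. At one-sided 0.2 the same move takes it from 0.95 to between 0.76 and 0.70.

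**The case against.** A reader might infer that the plan's only between-group test is the ANOVA group effect, so that the trial has about 30% power where it claims 95%. The documents do not support that, for four reasons.

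1. The Statistical analysis paragraph also names a between-group t test at 6 weeks, which is the kind of test that was powered.
2. The ANOVA gates only the within-group t tests. The 6-week comparison carries no such condition, so a null ANOVA would not block it.
3. The wording does not say main effect. It may loosely mean the interaction, whose power is 0.55 to 0.89 over the same correlations and equals that of the t test at r = 0.5.
4. Setting 0.27 to 0.33 against 0.95 charges the alpha change to the choice of test.

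Two further points are fair. The follow-up wording could imply a third assessment. With d = 0.8 at both post-baseline visits and equal correlations, the main effect would then have about 0.61, 0.52 and 0.45 power at r = 0.3, 0.5 and 0.7. That is still below the 6-week t test. Also, the unadjusted 6-week t test is a valid randomised comparison, so ANCOVA is the better choice here but not the only sound one.

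It can also be said that a statistical analysis plan, not shown here, might specify the ANOVA term. But the protocol itself attaches a purpose to the ANOVA, and its ordinary reading points to the main effect. It also puts a second test beside it without an order. Those statements, and the alpha conflict, are in the protocol and need correcting there.

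**Conclusion.** The point holds in a limited form. The stated power of 0.95 is correct arithmetic for one-sided alpha 0.2 and does not hold at the two-sided 0.05 the analysis uses. The 6-week t test then has about 0.69 power, and this result rests only on the protocol's own n and d, with d taken to apply at 6 weeks.

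The lower figure, about 0.33 to 0.27, is conditional. It applies if the first-named analysis is taken literally as the group main effect, with two time points, no baseline difference and r between 0.3 and 0.7. On that reading the test is badly aimed whatever the alpha.

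Group-by-time and ANCOVA also fall short of 0.95 over r = 0.3 to 0.7, though both would exceed it at r = 0.8 (0.97 and 0.98). The protocol gives no correlation on which to claim that.

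**What to change.** In the Statistical analysis paragraph, name one primary between-group test: the 6-week value compared by ANCOVA with group and baseline value, two-sided at 0.05. If the repeated-measures ANOVA is kept, name the group-by-time interaction as the treatment test. In either case, do not use the group main effect for that purpose, and state that any other between-group comparison is supportive.

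In the Sample size consideration and Power analysis paragraphs, restate power for the chosen test at two-sided 0.05 with 20 per group. That is about 0.69 for the unadjusted 6-week t test, or about 0.73 to 0.93 for ANCOVA with an assumed correlation of 0.3 to 0.7. If the interaction is chosen, it is 0.55 to 0.89 over the same range. State the correlation as an assumption, and say which outcome and time point d = 0.8 refers to.

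The cost is wording only, with no new data and no change in sample size. The downside is that the stated power becomes less favourable.

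### The sample size was computed at one-sided alpha 0.20 but the trial will test at two-sided 0.05, so the stated 95% power is about 69% for the test it was sized on

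*Protocol*

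**What the plan says.** Three places in the Protocol bear on the error rate.

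- **Sample size consideration (G*Power block).** The test is "Difference between two independent means (two groups"), run with one tail and these inputs: "Effect size d = 0.8", "α err prob = 0.2", "Power (1-β err prob) = 0.95", "Allocation ratio N2/N1 = 1". The output is a non-centrality parameter of 2.5298221, "Critical t = 0.8511828", 38 degrees of freedom, 20 per group and an actual power of 0.9531573.
- **Power analysis.** The calculation is restated in prose: "the sample size in respective group is calculated to be 20 patients with 95% confidence interval, power of 0.95 and effect size of 0.8". The paragraph adds that 20 patients in each group must complete follow-up for power to be adequate.
- **Statistical analysis.** "Statistical significance is determined by a two-sided p value of less than 0.05". A t test is among the tests named for comparing the primary and secondary outcomes between groups at 6 weeks, beside a two-way repeated measures ANOVA.

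**The concern.** The sizing calculation accepts a 20% false-positive rate in one direction. The analysis rule allows 5% in total, split over two directions. A 95% confidence interval, as named in the Power analysis paragraph, goes with the second rule and not the first. The power of 0.95 therefore belongs to a test that the trial will not run.

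This calculation is the only justification given for the number of patients. A reader of the Power analysis paragraph would conclude that a true effect of d = 0.8 would be missed only 5 times in 100. If the real figure is much higher, a non-significant result carries far less information than the Protocol suggests. That matters more here because the alternate hypothesis in the Hypothesis section covers the device being equal to conventional physiotherapy as well as better. A null result reported beside a claimed 95% power could be taken as support for equality. The Protocol does not say how a null result will be read, so this is a risk and not a stated intention.

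**Working it through.** **Inputs, all from the Protocol.** d = 0.8; n = 20 per group; 1:1 allocation; two-sample t test. Sizing level: one-sided 0.20. Analysis level: two-sided 0.05.

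**Formulae.** With n per group:

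- degrees of freedom: df = 2n − 2 = 38
- non-centrality: δ = d × √(n/2) = 0.8 × √10 = 2.5298
- critical value: t(1 − α, df) one-sided, or t(1 − α/2, df) two-sided
- power: probability that a non-central t with df and δ exceeds the critical value (for a two-sided test, plus the negligible lower tail)

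**Step 1: reproduce the printed figure.** At one-sided 0.20, δ = 2.5298221, critical t = 0.8511828 and power = 0.9531573, matching every digit printed. With 19 per group power is 0.9465, so 20 is the smallest size that reaches 0.95.

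**Step 2: could the 0.2 be a misprint?** Other levels at n = 20 per group and d = 0.8 do not fit the output:

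| Level | Critical t | Power |
| --- | --- | --- |
| One-sided 0.20 | 0.851 | 95.3% |
| Two-sided 0.20 | 1.304 | 88.9% |
| One-sided 0.05 | 1.686 | 79.9% |
| One-sided 0.02 | 2.127 | 65.7% |
| Two-sided 0.05 | 2.024 | 69.3% |

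Only one-sided 0.20 gives the printed critical value, so it was the level used.

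**Step 3: power under the trial's own rule.** At two-sided 0.05 the critical t is 2.0244 and power is 0.6934. The chance of missing d = 0.8 is 1 − 0.6934 = 0.3066, about 31%. The normal approximation gives 71.6%, so the result does not hinge on the method.

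**Step 4: which part of the mismatch matters most.** Moving from one-sided 0.20 to one-sided 0.05 costs 95.3 − 79.9 = 15.4 percentage points. Moving from one-sided to two-sided 0.05 costs a further 79.9 − 69.3 = 10.6. The alpha of 0.20 is the larger fault, but even one-sided 0.05 falls well short of 95%.

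**Step 5: what the design can do at two-sided 0.05.**

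- Size needed for d = 0.8: 26 per group for 80% power (80.7% achieved), 42 per group for 95% (95.2% achieved).
- Effect detectable with 20 per group: d = 0.91 with 80% power, d = 1.17 with 95%.
- If 18 per group are analysed (two losses per group, an illustrative assumption): δ = 0.8 × √9 = 2.40, critical t = 2.032, power 64.5%.

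**The case against.** The strongest objection is that 69% is the power of an unadjusted t test at 6 weeks, whereas the Statistical analysis paragraph first names a two-way repeated measures ANOVA. The power of its group-by-time term depends on the correlation between baseline and 6 weeks, which the Protocol does not give. Suppose d = 0.8 is the 6-week difference, baseline means are equal and the standard deviation is constant (all assumptions). The standardised difference in change is then 0.8/√(2(1 − r)), and power at two-sided 0.05 with 20 per group is 55% at r = 0.3, 69% at r = 0.5, 89% at r = 0.7 and 97% at r = 0.8. So 69% is not exact for every planned analysis. This stands as a limit on the figure. It does not rescue the printed 0.95: that number was computed for the independent-groups t test, the t test is also named for the 6-week comparison, and no correlation is offered to support a higher value.

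A second point is that every printed digit is correct for its inputs, so this is a mismatch of error rates and not a slip in calculation. That is true and leaves the conclusion unchanged.

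A third is that the loosely directional alternate hypothesis might explain the single tail. It does not explain an alpha of 0.20, and the Statistical analysis paragraph commits to two-sided testing. Nor could a separate analysis plan settle the matter, because the Protocol itself states the conflicting values.

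**Conclusion.** The concern holds. The sizing and analysis rules contradict each other, and the Power analysis paragraph attaches the 0.95 to an error rate that did not produce it. At two-sided 0.05, with 20 analysed per group, d = 0.8 and a two-sample t test at 6 weeks, power is 69.3% and not 95%. The chance of missing the target effect is about six times the stated one (31% against 5%). The figure assumes that all 40 patients complete and that the t test is the deciding comparison. Losses would lower it; the ANOVA figure could be lower or higher depending on an unstated correlation. The false power figure is the sole basis for the sample size and must be corrected.

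**What to change.** Keep the two-sided 0.05 rule. Replace the G*Power block and the power claim in the Power analysis paragraph with one consistent statement: with 20 analysed per group and a two-sided alpha of 0.05, a two-sample t test at 6 weeks has 69% power for d = 0.8, and 80% power for d = 0.91. Delete the reference to a 95% confidence interval and a power of 0.95. Say that these figures require 20 completers per group, and give the power under a plausible loss (for example, 64.5% with 18 per group).

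If the analysis is changed to adjust for baseline, power may be quoted for a stated correlation. At an assumed r = 0.5 the effective d is 0.8/√(1 − 0.25) = 0.924, and power with 37 degrees of freedom is about 81%. The assumption must be labelled as one.

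The cost is the rewording of two paragraphs and a less favourable stated power; no extra patients are needed. If the sponsor wants 80% or 95% power for d = 0.8 with the unadjusted t test, that is a separate choice needing 26 or 42 analysed per group (52 or 84 in total).
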